## Abstract

**Background:**

Pakistan observes a very high i.e. 37 percent modern contraceptive method related discontinuation rates within 12 months of their initiation. And almost 10 percent of these episodes of discontinuation happened due to the side effects or health concerns experienced by the women. Most importantly, it was noted that more than 12,000 first-level care facilities are located in the rural areas, including rural health centers, basic health units, and family welfare centers, but more than 30% of these facilities are nonfunctional. This paper presents a study protocol and participants’ profiling of a prospective cohort follow-up to compare the effectiveness of household based and telephonic approaches in sustaining the use of Long Acting Reversible Contraceptives (LARC) whilst to facilitate lowering method related discontinuation and increasing switching amongst the contraceptive users.

**Methods:**

A 12-month multi-centre, non-inferiority prospective user follow-up is employed using three different study categories: a) household based follow-up; b) telephonic follow-up; and c) passive or need-based follow-up along with the hypothetical assumption that the telephonic client follow-up is not inferior to the household based follow-up by continuation rate of LARC and the telephonic follow-up is less-costly than the household based client follow-up. This follow-up will be conducted in 22 health facilities – (16 rural and 6 urban based facilities) in district Chakwal. The first two study categories will receive scheduled but different follow-up from the field workers at 1, 3, 6, 9, and 12 month while the third one i.e. the ‘passive or need-based follow-up’ will serve as a control group. Using sampling software PASS 11, it was estimated to have 414 clients in each study category and around 1366 clients will be recruited to account for 10% attrition rate.

**Discussion:**

The study will help us to examine a more convenient method of effective follow-up for managing side effects, decreasing method discontinuation and increasing switching amongst users. The study information will also facilitate to develop a robust, effective and efficient mechanism for client follow-up to promote the continuation rates of LARC methods. The follow-up results and lessons learnt will be widely shared with stakeholders for their implementation and streamlining in health system.

## Background and context

Family planning (FP) is considered as one of the most cost effective interventions and has an imperative function to reduce maternal, infant and child health related morbidity and mortalities - as such that it has the potential to prevent around 30% of maternal deaths and 10% of child deaths [1, 2]. But the benefits of family planning are not limited just to promoting maternal or child health but can significantly influence enhanced opportunities for higher socioeconomic status, education, employment and empowerment especially for girls and women [3]. Likewise, family planning/contraception use also reduces the rates of unskilled unsafe abortions by preventing the mistimed or unwanted pregnancies [2].

But unfortunately, almost 300,000 women died only in 2013 due to pregnancy related complications which were avoidable [4, 5] and the preventable causes such as hemorrhage, hypertension and infections accounted for 56.8% of all maternal deaths [6]. It was noted that in the absence of contraceptive use, these deaths are projected to be almost two-fold higher [7].

In Pakistan, the lifetime risk of maternal death is one in 170 for women [8], and Pakistan is one of the six countries in the world anticipated to contribute to over half of all maternal deaths and complications of pregnancy and childbirth remain the leading cause of death and disability for childbearing women in Pakistan [9].

During the past 22 years, there is a three-fold progressive but gradual increase in the contraceptive use in Pakistan i.e. from 12 percent in 1990–91 to 30 percent in 2006–07 and then to 35 percent in 2012-13 [10, 11]. Likewise, the unmet need for family planning decreased from 31 percent to 20 percent during this period. But very unfortunately, modern contraceptive use remain as low as at 26 percent in contrast to the extremely high and favorable universal knowledge of contraception (almost 99%) with more dependency on short term, traditional and permanent methods of contraception [10]. Most importantly, the use of highly effective long acting reversible contraceptives (LARC) such as IUD and implant has remained almost negligible for a decade [1, 12].

The country also observes high contraceptive discontinuation rates of 37 percent within 12 months of their initiation resulting in particular from the side effects or health concerns associated mainly with short term modern contraceptives such as injections, pills and condoms [10].

In Pakistan, in a recent retrospective study in 2011 the contraceptive users revealed high IUD discontinuation among users (16.3% at 12 months) [13] while the implant 1-year discontinuation stands at 10% [14]. Importantly, the recent demographic survey reported a very high 26% of IUD discontinuation rate at 12 month. However, the main reason cited for IUD discontinuation was side effects in almost all the cases [10, 13, 14].

To promote modern family planning methods especially LARC methods, Marie Stopes Society (MSS), a local non-governmental organization in Pakistan, implemented a research project titled “Meeting the birth spacing needs of the underserved in Punjab province in Pakistan” and used demand-side financing – (DSF) through vouchers and expanding the *Suraj* health providers model (a Social Franchise (SF) network of health providers) as a two-pronged approach in order to increase the use and uptake of modern contraceptives [15]. Earlier evidence suggests that the DSF vouchers and social franchising; as an integrated approach used for LARC choices, has the potential to increase awareness and use of LARC methods [16, 17].

In the MSS Pakistan implemented research project titled “Meeting the birth spacing needs of the underserved in Punjab Province in Pakistan” the Field Health Educators (FHE) are working as a Community Health Worker within the *Suraj* model and has a similar role to a Lady Health Worker – LHW (LHW Programme is a Government of Pakistan owned Primary Health Care Initiative) and covers a population of around 20,000 to 25,000 spread over 3 – 6 kilometer radius [15]. This population catchment is far higher compared with the population and catchment areas of LHWs and Community Midwives – CMWs (CMW programme is a Maternal, Newborn and Child Health Initiative of the Government of Pakistan mainly for the population residing in the most far-flung rural areas) [15]. Each LHW serves a population of 1,000 people in their rural community while one CMW stationed for 5000 - 10,000 populations [15, 18–20]. This makes it challenging for FHE to frequently pay household based follow-up visits to the clients.

A large number of systematic reviews have documented the important role of community-based interventions including the household-based visits by community health workers to improve maternal and newborn health outcomes [21]. Likewise, several studies have cited that by strengthening the counseling and follow-up services component of the family planning programs will support women’s continuation of effective methods and ensure higher quality of services [22–24]. For example, a pool of studies have attempted to measure the effects of different approaches of user follow-up such as an scheduled visit at the clinic or a follow-up telephone contact and have reported mixed results; however, these studies has design and quality limitations [25]. Another study identified the importance of follow-up at six weeks for detecting early expulsion but the same study did not found any significant association between the regular visits and fewer pregnancies or expulsions [26]. Amongst those who cited medical reasons for the removal of IUD, there was a significant difference between the more frequent follow-up users as compared to the fewer scheduled follow-up as the earlier had a longer period of IUD continuation [26]. However, effect of a follow-up telephone call was not found as significantly different [27–30]. Unfortunately, sparse evidence is available on utility of household or telephone based client follow-up for family planning in Pakistan and in the neighboring countries.

Thus, there is a need to study effects of prospective follow-up to the end-user and counseling related to side-effect management by a provider or community health worker in the rural setting in Pakistan. Therefore, we propose to conduct a prospective cohort follow-up to compare the effectiveness of household based and telephonic approaches in sustaining the use of LARC among SF clients. Very recently, the Department of Reproductive Health and Research at the World Health Organization in Geneva unveiled the 15 highest priority topics as their global agenda to promote family planning research [2]. Amongst those identifying main barriers to the uptake and use of modern contraceptive in low prevalence settings and the determinants of the discontinuation as well as switching of contraceptive methods seem extremely relevant and timely for our study [2]. In addition, engagement with the private sector through franchising; task shifting and impact of financing schemes on quality are also pertinent for our study [2].

Following are research questions, hypothesis and list of measurement indicators of the proposed study:

**Research Question**Is telephonic client follow-up on LARC continuation is as effective as the effect of (gold standard) active household based client follow-up?Is the telephonic client follow-up less costly compared with the household based client follow-up?

**Hypothesis**The telephonic client follow-up is not inferior to the household based follow-up by continuation rate of LARC.The telephonic client follow-up is less-costly than the household client follow-up.

**List of follow-up measurement indicators**The cumulative probability of LARC discontinuation 1, 3, 6, 9, and 12 months by study arms.The reasons for LARC discontinuationLevel of client satisfaction with the counseling received from FHE by study armsThe proportion of clients lost to follow-upCost per telephonic call and per household based visitTime duration per callLevel of difficulty faced by client in contacting FHE by follow-up group

## Methodology

The present study is nested in the larger research project - Meeting the birth spacing needs of the underserved in Punjab Province in Pakistan [15].

### Design

A multi-centre, prospective non-inferiority trial.

### Scope

This 12 month follow-up from December 2013 – December 2014 will be conducted only in Chakwal district nested under the routine monitoring of programme activities on Demand Side Financing [15]. A total of 22 centers will be included in this follow-up, of which 16 are mid-level providers branded as Suraj (i.e. in English, called Sun, is a brand provided to the clinics of the trained providers of MSS) and located in rural periphery, while the 6 are medical doctors based in peri-urban or urban areas.

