### Follow-up cohorts

The recruitment of follow-up participants will take place under three different categories: a) household based follow-up; b) telephonic follow-up; and c) passive or need-based follow-up, serving as control group. The clients recruited under category ‘a’ will receive a scheduled follow-up from FHE at 1, 3, 6, 9, and 12 month. Similarly, the clients recruited under category ‘b’ will receive a telephone call from FHE at the scheduled frequency similar to category ‘a’. In addition, the participants of both the categories (‘a’ & ‘b’) can also seek medical advice from FHE based on need (unscheduled contact). While, category ‘c’ participants will not receive any scheduled intervention from FHE but can only seek FHE’s assistance in case of any medical need.

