### Sample size

In order to detect 6% difference amongst the categories, with an 80% power and using sampling software PASS 11, it was estimated to have 414 clients in each of the three groups. Around 1366 clients will be recruited to account for 10% attrition rate. Based on services statistics the estimated sample can be achieved if all the clients at each clinic (who gives informed consent) are registered during the (specified) period for 3-4 months. Thereby clinics having high clientele will contribute more to the sample (to hold proportionality assumption).

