### Sampling strategy

Based on preliminary data taken from the field, it is estimated that around 40% of the LARC users have mobile phones [31] thus due to shorter recruitment time, selection of follow-up participants will be done following consecutive sampling. The reason for selecting consecutive sampling over randomization was mainly the long recruitment periods and the budgetary implications. After screening, all the clients receiving LARC during 3-4 months (Nov 2013 till Feb 2014) period will be briefed about follow-up and invited to participate in the follow-up based on their informed consent. Clients will be asked to voluntarily choose the group (among the three described above) under which she would like to be enrolled. Once the desired sample of any specific group is achieved, that group will be eliminated as an option for subsequent clients to opt for. A format will be given to each service provider to keep a track of client enrollment under each group. The same information shall be recorded on the baseline and follow-up form so as to ascertain the selection is performed as per the protocol.

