### Implementation

Once the client adopted the LARC, she will be asked to participate in the follow-up. As described above, the women enrolled under the active categories (‘a’ & ‘b’) will receive counseling on side-effect management, through an adapted manual used in the Family Advancement for Life and Health (FALAH) project [32] at 1, 3, 6, 9 and 12-month post IUCD insertion. The FALAH was a family planning project supported by the United States Agency for International Development (USAID) whose aim was to protect the health and well being of mothers, newborns and children through the adoption of birth spacing by eligible couples in Pakistan [33]. The same manual will be used to assist women with side-effect management as per need. In order to minimize dropouts/lost-to-follow-up, all the clients will be informed about the detailed follow-up procedures, while taking informed consent. For schedule visits, the FHEs will be reimbursed for their transportation cost. Similarly, FHEs will also be paid for telephone call expenses.

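### Follow-up is dated to December 2014, but enrolment runs to February 2014 and contacts run to 12 months after insertion, so January–February 2014 clients cannot reach month 12 inside the stated window

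*Protocol article*

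**What the plan says.** Four parts of the protocol article bear on the calendar.

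- **Scope:** "This 12 month follow-up from December 2013 – December 2014 will be conducted only in Chakwal district". No day of the month is given for either end.
- **Sampling strategy and Sample size:** those invited are "all the clients receiving LARC during 3-4 months (Nov 2013 till Feb 2014) period". The Sample size section likewise says that consenting clients "are registered during the (specified) period for 3-4 months".
- **Follow-up cohorts and Implementation:** clients in the household group "will receive a scheduled follow-up from FHE at 1, 3, 6, 9, and 12 month", and the telephone group has the same timetable. Time starts at each woman's own procedure, because counselling in both active groups is given "at 1, 3, 6, 9 and 12-month post IUCD insertion" and recruitment happens at adoption: "Once the client adopted the LARC, she will be asked to participate in the follow-up".
- **Indicators (end of Background and context):** the first on the list is "The cumulative probability of LARC discontinuation 1, 3, 6, 9, and 12 months by study arms".

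The Limitations section adds that data are collected straight after the 12-month visit. Nowhere does the article extend follow-up into 2015, give a common closing date with censoring, or state a tolerance around a visit.

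**The concern.** Three statements cannot all be true: enrolment to the end of February 2014, a contact 12 months after every insertion, and follow-up that ends in December 2014. The start date is not at fault, since November enrolees have their month-1 contact in December 2013. Only the end date conflicts.

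The non-inferiority hypothesis is about LARC continuation, and month 12 is the last time point at which it is measured. If field staff took the Scope dates literally, later enrolees would be handled in one of three ways: left out of the 12-month result, interviewed early and counted as month 12, or censored. The article does not choose, and the three differ in precision and bias.

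There is also a possible link to the groups. Under the Sampling strategy, "Once the desired sample of any specific group is achieved, that group will be eliminated as an option". If groups filled at different times, late enrolees would be concentrated in whichever groups were still open, and shortened follow-up would then differ by group.

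**Working it through.** **1. Dates side by side.** Month-12 date = insertion date + 12 months.

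| Enrolled | Month 12 falls in | Inside December 2013–December 2014? |
|---|---|---|
| November 2013 | November 2014 | yes |
| December 2013 | December 2014 | yes, if the window runs to 31 December |
| January 2014 | January 2015 | no |
| February 2014 | February 2015 | no |

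**2. Share affected.** Accrual by month is not documented, so even accrual is assumed. Share = enrolment days whose month-12 date falls after the close, divided by all enrolment days.

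| Enrolment assumed | Close assumed | Share after close |
|---|---|---|
| 1 Nov–28 Feb | 31 Dec 2014 | 59/120 = 49% |
| 1 Nov–28 Feb | 15 Dec 2014 | 75/120 = 62.5% |
| 1 Nov–28 Feb | 1 Dec 2014 | 89/120 = 74% |
| 1 Nov–31 Jan | 31 Dec 2014 | 31/92 = 34% |
| 15 Nov–14 Feb | 31 Dec 2014 | 45/92 = 49% |
| 30 Nov–28 Feb | 31 Dec 2014 | 59/91 = 65% |

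Changing one element at a time gives 34% to 74%. Pairing the latest three-month enrolment with a 1 December close would push it to 89/91 = 98%. Front-loaded accrual would lower every figure. At 49.2%, the count is about 620 of the 424 + 409 + 428 = 1,261 women profiled at baseline, or 672 of the 1,366 planned.

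**3. Follow-up actually available.** With a 31 December close, a client enrolled on 28 February has about 10 months. Affected clients average about 11 months.

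**4. Effect of each way of handling them.** The document gives neither the assumed discontinuation rate nor the significance level. I assume 14% in both groups, one-sided 5%, the stated 6 points as the margin, and constant hazard. Group sizes are 424 (telephone) and 409 (household).

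*No truncation.* SE = √[0.14 × 0.86 × (1/424 + 1/409)] = 0.0240. Power = Φ(0.06/0.0240 − 1.645) = Φ(0.85) ≈ 80%.

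*Affected clients dropped.* The share kept is 61/120 = 0.508, so 424 × 0.508 ≈ 216 and 409 × 0.508 ≈ 208. SE = √[0.14 × 0.86 × (1/216 + 1/208)] = 0.0337. Power = Φ(0.06/0.0337 − 1.645) = Φ(0.135) ≈ 55%.

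*Affected clients right-censored at 31 December.* Integrating the Greenwood variance with censoring spread over months 10 to 12 raises the variance at month 12 by a factor of about 1.07. SE = 0.0240 × √1.07 ≈ 0.0248. Power = Φ(0.06/0.0248 − 1.645) = Φ(0.77) ≈ 78%.

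*Last interview counted as month 12.* At 11 months, 1 − 0.86^(11/12) = 12.9%. Over the whole cohort, 0.508 × 14% + 0.492 × 12.9% ≈ 13.5%. If the other group's true rate were 20%, the same steps give 1 − 0.80^(11/12) = 18.5% and a cohort figure of about 19.3%. A true 6-point difference would then appear as about 5.8 points.

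**5. Sensitivity to the assumed rate** (6 points, one-sided 5%). The 10%, 16.3% and 26% are the implant and IUD 12-month figures quoted in the Background.

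| Rate | No truncation | Dropped | Censored |
|---|---|---|---|
| 10% | 89% | 66% | 88% |
| 14% | 80% | 55% | 78% |
| 16.3% | 76% | 51% | 73% |
| 26% | 63% | 41% | 60% |

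The absolute level depends heavily on the assumed rate. The pattern does not: dropping these clients costs about 22 to 25 points of power, and censoring costs about 2 to 3.

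**The case against.** The strongest defence is that the Scope dates are only nominal. The Implementation section already ties each contact to the woman's own insertion, and the Limitations section places final data collection after the 12-month visit. On that reading the individual schedule is the more specific rule, the last contacts simply run into early 2015, and nobody is truncated. This may well be what was intended, and it means that month 12 needs no new definition. It does not remove the conflict, because the only end date printed is December 2014. It does reduce the remedy to little more than a corrected date.

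Censoring rules and visit tolerances can also fairly be left to a fuller document. The point here is not their absence but that two printed date ranges disagree.

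Three stronger readings are tempting, and the document does not support them:

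- **That the trial will lose half its outcomes and its power will fall to 55%.** This needs even accrual, a real stop on 31 December, and every affected client discarded despite 10 to 12 months of observation. The listed outcome is a cumulative probability, to which partial follow-up can contribute.
- **That early interviews would tilt the result materially towards non-inferiority.** The direction is right, but cohort-wide the shift is about half a point. The 11.8% obtained from 1 − 0.86^(10/12) applies only to the last client enrolled. No section provides for labelling an earlier interview as month 12.
- **That truncation does differ by group.** No fill dates are given. If the target per group was 1,366/3 ≈ 455, no group reached it (424, 409, 428) and the closing rule never applied. If it was 414, the telephone and passive groups could have closed. Unequal truncation is possible but not shown.

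**Conclusion.** The inconsistency stands and needs no outside source: on any reading of the Scope dates, a client enrolled in January or February 2014 has no month-12 contact by December 2014. How many clients this touches is an assumption-based estimate, because accrual by month is not reported. It is about half under even accrual and the most generous closing day.

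The consequence is conditional on the December 2014 close being applied. Discarding the affected clients would be a serious loss of precision. Censoring them would cost little, and early interviews counted as month 12 would bias the rate slightly downwards. The power figures also depend on an assumed 14% rate, one-sided 5%, and the stated 6 points serving as the margin. It is worth correcting because month 12 carries the non-inferiority question and the correction is cheap.

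**What to change.** Reconcile the Scope section with the Sampling strategy and Implementation sections by stating that data collection closes 12 months after the last enrolment, about the end of February 2015. The existing anchoring of contacts to insertion can stay as it is. The cost is about two more calendar months of contacts that these clients have already been promised.

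If fieldwork has to close in December 2014, say so and add three things:

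- right-censor each client at the actual time from insertion to last contact;
- do not count any interview before month 12 as a month-12 outcome;
- report, by group, the number with full 12-month data, which would also show whether truncation differed between groups.

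That route costs one censoring rule and one extra line in the results.
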